The target population of the quantitative component of the study is women aged 15-49 years who reside at the study sites. The participants will be women who gave birth within 12 months at the time of both the baseline and endline surveys. Women whose births resulted in stillbirths, those who did not consent to participate in the surveys, or those who faced a language barrier with surveyors - due to the presence of ethnic minorities who speak different local languages - will not be enrolled. In contrast, the qualitative component targets additional groups, such as village health volunteers and workers, male partners, family members, and health center staff.

Sample size and sampling method

We estimated the sample size using the logistic regression formula n > 10 m, where the minimum "n" of respondents with or without the study outcome is 10 times the number of covariates "m" to be included in the regression [30]. We estimated at least 80 facility-based follow-up PNC users with eight potential covariates. In 2022, VHVs/VHWs reported that there were 302 children of ≤1 year of age in the 37 targeted villages, including 137 from the 19 villages in Sepone and 165 from the 18 villages in Vilabuly. Due to the relatively low yearly delivery at the target sites, we will conduct exhaustive sampling at the baseline to include all eligible subjects, ensuring representative results [31].

For the end-line survey, we estimated the required sample size for difference-in-differences analyses to assess changes in the primary outcome before and after the intervention. We anticipate a 15.0% increase in facility-based follow-up PNC in the intervention villages and a 5.0% increase in the control villages over two years of implementation. Using a two-tailed z test for the difference between proportions, with 80% statistical power at the 5% significance level, unequal cluster size assessment, a design effect of 2, and a non-response rate of 10%, we estimated a sample size of 302 for the end-line survey [32,33].

Finally, at least 12 participants will be selected purposively for interviews in the qualitative component [34]. The enrollment of further participants will depend on when data saturation is reached.

Intervention, monitoring, and assessments

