## Results

At the end of the study, several outcomes are anticipated in line with the study objectives. First, assuming baseline utilization is about 5% in both districts, we expect a 15% increase in Sepone (intervention) and a 5% increase in Vilabuly (control), resulting in a 10% difference in the proportion of women receiving at least one facility-based follow-up PNC visit. Second, guided by the theory of change, we hypothesize this improvement to result from enhanced counseling and more frequent interactions between mothers, male partners, and VHVs/VHWs through a gender-norms-sensitive approach. Specifically, regular household visits by paired VHVs/VHWs are expected to strengthen trust and satisfaction among mothers and promote male partner involvement, thereby contributing to increased PNC service uptake. Lastly, we also anticipate a longer average duration of postpartum facility stays among mothers in intervention areas.

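### The end-line sample size of 302 does not give the stated 80% power for the 10-point difference-in-differences; power is about 31% to 54%, depending on the design effect

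*Protocol article*

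**What the plan says.** In Materials and methods, under sample size and sampling method, the end-line calculation has an explicit purpose: "we estimated the required sample size for difference-in-differences analyses to assess changes in the primary outcome before and after the intervention". The effect is given as changes: "We anticipate a 15.0% increase in facility-based follow-up PNC in the intervention villages and a 5.0% increase in the control villages". The test and error rates are stated as "Using a two-tailed z test for the difference between proportions, with 80% statistical power at the 5% significance level". The section adds an allowance for unequal cluster sizes, a design effect of 2 and 10% non-response, and ends with "we estimated a sample size of 302 for the end-line survey". It does not call this a per-arm number.

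The same section reports that in 2022 "there were 302 children of ≤1 year of age in the 37 targeted villages", 137 in Sepone and 165 in Vilabuly, and plans exhaustive sampling at baseline.

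The Results section supplies the remaining input, "assuming baseline utilization is about 5% in both districts", and the scale of the effect, "resulting in a 10% difference in the proportion of women receiving at least one facility-based follow-up PNC visit". The end-line levels are therefore 20% and 10%. The data analysis section tests the effect by difference-in-differences and by a time-by-group interaction in a mixed-effects logistic model.

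**The concern.** A difference-in-differences carries sampling error from four proportions, two per survey round. A z test for two proportions carries it from only two. The article names the first as the analysis and the second as the sizing method, and the required end-line number equals the count of young children already reported for the villages.

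The power statement for the primary outcome is at stake. Readers are told that a true 10-point gain would be detected four times in five. If the real figure is far lower, a non-significant result carries much less information than the article implies, and the study is intended to inform national primary health care strategy.

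**Working it through.** **Inputs.** From the sample-size section: increases of 15 and 5 points, two-sided 5%, 80% power, design effect (DE) 2, non-response 10%, 137 and 165 women. From Results: baseline 5% in both districts. (1.960 + 0.842)² = 7.849.

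**1. Reproducing 302.** Enter 15% and 5% as end-line levels, with unpooled variance:

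n per arm = 7.849 × (0.15×0.85 + 0.05×0.95) / 0.10² = 7.849 × 0.175 / 0.01 = 137.4

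137.4 × 2 × 1.1 = 302.2

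If the 2 is the design effect, 302 is per arm and the survey needs about 604. If the 2 counts the arms, 302 is a total and the design effect was left out. In both cases the increases have been used as levels and baseline sampling error is absent.

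**2. Power for the difference-in-differences.** With 137 and 165 women in each round:

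Var = DE × [(0.05×0.95 + 0.20×0.80)/137 + (0.05×0.95 + 0.10×0.90)/165]
= DE × [0.2075/137 + 0.1375/165] = DE × 0.002348

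Power = Φ(0.10/SE − 1.96)

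| | SE | 0.10/SE | Power | Power after 10% non-response |
|---|---|---|---|---|
| DE 1 | 0.0485 | 2.06 | 54% | 50% |
| DE 2 in all four cells | 0.0685 | 1.46 | 31% | 28% |

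**3. The planned logistic interaction.** The odds ratio for 5% to 20% is 4.75 and for 5% to 10% is 2.11. Their ratio is 2.25, and ln 2.25 = 0.811. The Wald SE, from the sum of 1/[n p(1−p)] over the four cells, is 0.628 (DE 1) or 0.888 (DE 2). Power is about 25% or 15%.

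**4. Other readings of 302 at DE 2.**
- 302 per arm at end-line, with the baseline at 137 and 165: 46% (42% after non-response).
- 302 per arm in both rounds: 55% (51% after non-response).
- End-line-only comparison of 20% with 10%, 302 in total: about 40%.

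Only an end-line-only comparison of 15% with 5%, with no design effect, passes 80% (about 82% unpooled, before non-response). It conflicts with the stated analysis, the stated design effect and the Results levels.

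**5. Difference detectable with 80% power.** Hold the baseline at 5% and the control end-line at 10%, let the intervention end-line be 10% + d, and solve d = 2.802 × SE(d). This gives d = 14.0 points at DE 1 and 20.7 points at DE 2. Holding the SE at its 10-point value would give 13.6 and 19.2, which is too small because the variance grows with d.

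**6. Size needed for 80%.** 7.849 × (0.0475 + 0.0475 + 0.16 + 0.09)/0.01 = 271 per arm per round. × 2 (DE) = 542; / 0.9 = 602 per arm, or about 1,203 women in each round.

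**The case against.** **The design effect.** The same 37 villages are surveyed twice, so stable village effects partly cancel in a difference-in-differences. The article states its design effect alongside a two-proportion test and does not say that it carries over unchanged. This stands: 31% is the conservative end, not the single answer. A reader might infer that power is well under half of the 80% claimed, or that a non-significant result is the expected outcome. Neither follows, since with no design effect power is 54%.

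**The origin of 302.** The article condenses a method taken from references that are not shown, and its handling of unequal clusters is unexplained. Other routes come close. A pre-post comparison of 5% with 20% by the arcsine formula needs 69.2 per group, and 69.2 × 2 × 2 × 1.1 is about 305. So a reader cannot take it as shown that the sponsor entered increases as levels; that is only the simplest explanation. It does not rescue the figure, because none of the difference-in-differences readings computed here reaches 80%.

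**The end-line pool.** A reader might conclude that the villages cannot supply 302 women after non-response and exclusions. The 302 is a volunteer report from 2022, the end-line births come later, and exhaustive sampling is stated only for baseline. A similar end-line pool is an assumption.

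**The harm.** Nothing in the article says that a null result would be read as evidence against the policy, and it already commits to reporting 95% confidence intervals. The consequence is mainly one of disclosure, which still matters because the power statement is wrong as written.

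**Conclusion.** The concern holds. As an end-line total, 302 does not give 80% power for a 10-point difference-in-differences. On the article's own levels and village counts, power is about 31% with the design effect of 2 in all four cells and about 54% with none, or 28% and 50% after the stated non-response. On the interaction term of the planned logistic model it is lower still, about 15% to 25% by a Wald approximation.

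Three assumptions carry these figures: each round yields about 137 and 165 women, as in the 2022 count; the baseline is 5% in both districts; and the true design effect for the difference-in-differences lies between 1 and 2. The conclusion does not depend on how 302 was derived, and reading it as a per-arm number lifts power only to 42% to 55%.

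**What to change.** Keep the exhaustive sample and replace the 80% power and 302 statement with wording such as:

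> All eligible women, about 302 per round, will be surveyed. Power for a 10-point difference-in-differences from a 5% baseline is about 31% (design effect 2) to 54% (design effect 1), slightly lower after 10% non-response. The difference detectable with 80% power is about 14 to 21 points.

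Label the end-line count as an assumption based on the 2022 report, and give the end-line levels (20% and 10%) beside the increases. State that the primary result will be interpreted through the difference-in-differences estimate and its 95% confidence interval.

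The cost is rewording only, with no added women or fieldwork. The price is a less favourable power statement.

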## Abstract

Background: Despite substantial improvements in antenatal care and skilled birth attendance coverage, postpartum service uptake lags in the Lao People's Democratic Republic (Lao PDR). The 2019 Lao Primary Health Care Policy emphasizes the importance of village health volunteers/workers (VHVs/VHWs) working as groups or pairs to promote primary care services, including obstetric care. However, little is known about whether or how the pairing of male and female VHVs/VHWs may encourage better uptake of postpartum care in communities with solid gender norms.

Objective: Therefore, the study aims to assess the effectiveness of male-female VHVs/VHWs working in pairs on women's uptake of facility-based follow-up PNC visits in rural Sepone, Lao PDR.

Methods: A quasi-experimental cluster study will be conducted between July 2024 and October 2026 in 37 selected sites from two districts in the southern Lao PDR. In 19 selected intervention villages in the Sepone district, trained female-male VHVs/VHWs pairs will promote postpartum services, whereas in 18 similar control villages in the Vilabuly district, VHVs/VHWs will implement standard activities for obstetric care promotion. The study obtained ethical approvals from the University of the Ryukyus and the Lao Tropical and Public Health Institute.

Data analysis: Difference-in-difference analyses will be conducted to estimate service coverage pre-post intervention changes in study sites. Then, using mixed-effect binary logistic regressions, we will assess the association between pairing VHVW/s and facility-based follow-up PNC use, which will be adjusted for other covariates and time effects. Finally, we will analyze the context of pairing VHVs/VHWs implementation using coded transcripts of interviews and focus group discussions.

Results: At the end of the study period, we anticipate at least a 10% increase in follow-up PNC visits at intervention sites compared to control sites. The improvement is expected to result from improved mothers' trust and satisfaction with VHVs/VHWs, and enhanced husband support.

Conclusion: The findings of this study will guide the Lao government's strategy to involve both male and female VHVs/VHWs in primary healthcare according to the 2019 Primary Health Care Policy.

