To monitor implementation fidelity, VHVs/VHWs will complete standard reporting forms each month, documenting home visits and activities conducted. A midterm review using both monitoring data and qualitative insights will assess progress and inform any necessary course corrections.

Data collection

Both baseline and end-line assessments will be carried out using household surveys. Data will be collected by trained research assistants (medical students) using pretested semi-structured questionnaires prepared in English and translated into Lao using the Epi Info software. The questionnaires will be administered on tablets in Lao or other local languages as needed. The questions will focus on participants' socioeconomic and demographic characteristics, prior MCH service usage, and indicators of accessibility to healthcare facilities. Self-reported service utilization will be cross-validated using the maternal and child health handbooks (also known as the “pink book”).

Variables

WHO recommends that postpartum women have at least four postnatal care sessions regardless of delivery location, including within 24 hours after birth, on day 3, between seven days and 14, and after six weeks [11]. The primary outcome of the quantitative component is the use of at least one facility-based follow-up PNC visit within six weeks postpartum (yes/no). The secondary outcome is the duration (in hours) of facility-based postpartum stay by mothers after delivery. The two main predictor variables identified include residing in intervention versus control villages, and the frequency of VHVs/VHWs visits to mothers [36]. Additional variables will include respondents' sociodemographic characteristics, husbands' characteristics, household characteristics, gender norms, and trust in VHVs/VHWs.

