Qualitative data will be gathered through key informant interviews and focus group discussions (FGDs). Interview and FGD guides will be developed in Lao, and interviewers (medical students) will receive training in qualitative data collection techniques. With participants’ consent, all interviews and discussions will be audio recorded, anonymized, and securely stored on a drive accessible only to the research team. The qualitative study will be conducted during the implementation phase to examine how the intervention is delivered and perceived, and to gain insights into the processes influencing its effectiveness. Interview and discussion guides will focus on the dynamics of interactions between VHVs/VHWs and mothers, between VHVs and mothers’ family members, and among VHVs who work together.

Data analysis

We will conduct difference-in-differences analyses using estimated levels of key indicators before and after the intervention, and test the significance of changes in outcomes. Pearson chi-square tests or t-tests will be used, as appropriate, to compare gaps in service use based on women's characteristics and other covariates. For multivariate analyses, mixed-effects logistic regression will be used to evaluate the associations between the primary outcome and predictor variables, while including interaction terms between time and group to assess the intervention effect. Statistics will be reported along with their 95% confidence intervals. P values of <0.05 will be considered to indicate statistical significance. All analyses will be performed using Stata Statistical Software (release 17, 2021, StataCorp, College Station, TX).

For the qualitative component, interview and FGD audio recordings will be transcribed, translated into English, and analyzed using both inductive and deductive content analysis approaches. Relevant codes will be extracted and organized into themes and sub-themes to provide insights into the intervention’s implementation context, feasibility, and acceptance within the community.

Ethical considerations

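### The planned regression appears to condition the time-by-group effect on VHV/VHW visit frequency, a stated mechanism of the intervention, so the only covariate-adjusted estimate is pulled towards the null

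*Protocol article*

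**What the plan says.** All references are to the protocol article.

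- **Materials and methods, Variables.** Two main predictors are named: "The two main predictor variables identified include residing in intervention versus control villages, and the frequency of VHVs/VHWs visits to mothers". A further sentence lists other variables without assigning them to any model: "Additional variables will include respondents' sociodemographic characteristics, husbands' characteristics, household characteristics, gender norms, and trust in VHVs/VHWs".
- **Materials and methods, Data analysis.** The regression is to "evaluate the associations between the primary outcome and predictor variables, while including interaction terms between time and group to assess the intervention effect". A difference-in-differences analysis on estimated levels before and after the intervention is planned as well, and no covariates are mentioned for it.
- **Abstract, Data analysis.** The regression comes after the difference-in-differences analysis and concerns the association between pairing and follow-up PNC use, "which will be adjusted for other covariates and time effects".
- **Sample size and sampling method.** "We estimated at least 80 facility-based follow-up PNC users with eight potential covariates". The eight are not named.
- **Intervention, monitoring, and assessments.** Women at all sites receive regular visits, but a minimum visit schedule is set out for intervention sites only.
- **Results.** The improvement is expected to come from better counselling and more frequent interactions. Further, "regular household visits by paired VHVs/VHWs are expected to strengthen trust and satisfaction among mothers and promote male partner involvement", which is expected to raise uptake.

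**The concern.** Visit frequency has two roles that conflict. In the Variables and Data analysis sections it is a predictor in the model that is to yield the intervention effect. In the Intervention and Results sections it is something the intervention delivers and a route by which uptake should rise. A variable that lies between the intervention and the outcome is a mediator. Holding it fixed removes the part of the effect that passes through it.

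The objective concerns the effectiveness of paired VHVs/VHWs on uptake, and the anticipated 10-point difference is a total effect. A time-by-group term conditional on visit frequency answers another question: how much uptake differs between women who had the same number of visits. The better the programme succeeds through visits, the smaller that term becomes. A real benefit could then be reported as small or absent in the adjusted analysis.

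**Working it through.** **Step 1. Is visit frequency in the effect model?** The Variables section calls it a main predictor. The Data analysis section puts predictor variables and the time-by-group interaction in the same regression. No section separates a total-effect model from a mechanism model or says that a direct effect is intended. The natural reading is one model containing both.

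**Step 2. Are the end-line values affected by the intervention?** Participants gave birth within 12 months of the survey in question. Baseline is July to September 2024, pairs were formed and trained by November 2024, and end-line is around July 2026. End-line respondents therefore gave birth from about July 2025 onwards. Their visit counts, and any trust or satisfaction they report, essentially follow the start of the intervention.

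**Step 3. The article's own effect size.** Baseline is 5% in both districts, with increases of 15 and 5 points (Results).

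- End-line rates: 5 + 15 = 20% (intervention) and 5 + 5 = 10% (control).
- Difference in differences: (20 − 5) − (10 − 5) = 10 points, which reproduces the anticipated difference.
- Interaction odds ratio: the common baseline odds cancel, leaving (0.20/0.80) / (0.10/0.90) = 0.250/0.111 = 2.25.

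**Step 4. What conditioning on visits does to it.** Let m be the share of the log odds ratio that runs through visits. To a close approximation the conditional odds ratio is 2.25^(1 − m), with ln 2.25 = 0.811. A large-sample logistic illustration (400,000 women, no random effects) was also run with assumed mean visits of 1.5 at baseline, 2.0 in control at end-line and 5.0 in intervention at end-line.

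| Share through visits (assumed) | 2.25^(1 − m) | Illustration, visits in model |
|---|---|---|
| 0% | 2.25 | 2.19 |
| 25% | 1.84 | 1.88 |
| 50% | 1.50 | 1.50 |
| 75% | 1.22 | 1.25 |
| 100% | 1.00 | 1.01 |

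Without visits in the model, the illustration stays at about 2.2 to 2.3 for every share.

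**Step 5. How strong would the visit effect have to be?** The assumed means give an excess change of (5.0 − 1.5) − (2.0 − 1.5) = 3.0 visits. Full mediation then needs an odds ratio per visit of about exp(0.811/3.0) = 1.31, and half mediation about exp(0.405/3.0) = 1.14. The article gives neither the visit means nor the share, so the table shows a range and is not a forecast.

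**The case against.** **Is it really one model?** This is a condensed article, and the model sequence and final covariate set may be fixed in a fuller document. That stands for the unnamed covariates. It is weaker for visit frequency, which the article itself names as a main predictor alongside group.

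**Trust and gender norms.** A reader might infer that these are also certain to be in the effect model. The text does not support that. The phrase "household characteristics, gender norms, and trust in VHVs/VHWs" comes from a list of study variables, and the eight covariates are unnamed. The Abstract's adjustment wording makes their entry possible, no more.

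**Is the effect adjusted away?** A reader might infer this too. It holds only under full mediation. The Results section also relies on counselling quality and male partner involvement, which the number of visits to mothers does not measure. Attenuation is the supported word.

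**Is the total effect lost from the study?** No. The difference-in-differences analysis on levels is listed first, the end-line sample size is built on it, and as described it does not condition on visits. What remains is that no covariates are mentioned for it, in a non-randomised comparison of two districts for which Strengths and limitations concedes selection bias and confounding. The regression is the only analysis described as covariate-adjusted.

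**Visits occur in both arms, so adjustment isolates pairing.** Whether pairing matters beyond the amount of contact is a fair question. It concerns a direct effect, and the article neither states it as the target nor excludes more frequent contact from the benefit expected of the intervention.

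**Conclusion.** The concern holds in limited form. Read together, the Variables and Data analysis sections place visit frequency, and possibly trust, in the regression whose time-by-group term is to give the intervention effect. Because the article makes visit frequency part of the intervention and its mechanism, that term is a direct effect and understates the total effect if visits raise uptake as expected.

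The size cannot be computed from the article. Starting from the implied odds ratio of 2.25, the adjusted estimate would be about 1.9, 1.5 or 1.0 if 25%, 50% or 100% of the effect ran through visits. This rests on the assumed shares and visit means, and on reading the anticipated increases as percentage points, which the stated 10% difference supports. Further bias from unmeasured factors that drive both contact or trust and care-seeking is possible, but it is conditional and is not quantified here.

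The study would still estimate an unadjusted total effect. The problem lies in the adjusted estimate, to which readers of a non-randomised study will give most weight.

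**What to change.** - State that the intervention effect is the time-by-group term from a mixed-effects logistic model with group, time, their interaction, village random effects, and only covariates that the intervention cannot change (for example age, parity, education, ethnicity or language, wealth and distance to a facility).
- Leave out of that model visit frequency, any other post-intervention VHV/VHW variables such as trust and satisfaction, and end-line gender norms.
- Analyse those variables in a separate model labelled as a mechanism (mediation) analysis. If the effect of pairing beyond contact volume is of interest, report it there and call it a direct effect.
- Report visit frequency by arm as a fidelity measure. The monthly VHV/VHW forms already record home visits.

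The cost is about two sentences in the Data analysis section and no new data. The change should be made before the end-line data are analysed.

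### The chi-square and t-tests named for covariate comparisons ignore village clustering that the plan itself assumes; a nominal 5% test runs at up to about 16.6% for village-level factors, and less for factors that vary within villages

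*Protocol article*

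**What the plan says.** All references are to the protocol article, Materials and methods, unless stated otherwise.

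- **Data analysis, bivariate tests.** "Pearson chi-square tests or t-tests will be used, as appropriate, to compare gaps in service use". The sentence goes on to say that these gaps are examined by the women's characteristics and other covariates. No cluster adjustment is attached.
- **Data analysis, threshold.** "P values of <0.05 will be considered to indicate statistical significance". Statistics are also to carry 95% confidence intervals.
- **Data analysis, intervention effect.** A mixed-effects logistic regression with time-by-group interaction is named for the primary outcome.
- **Data analysis, difference-in-differences.** Changes in outcomes are to be tested for significance. Neither the test nor its handling of clusters is stated.
- **Sample size and sampling method.** The calculation for the second survey uses "unequal cluster size assessment, a design effect of 2, and a non-response rate of 10%, we estimated a sample size of 302 for the end-line". The same paragraph sets out the planning test: "Using a two-tailed z test for the difference between proportions, with 80% statistical power at the 5% significance level".
- **Sample size and sampling method, expected numbers.** "302 children of ≤1 year of age in the 37 targeted villages, including 137 from the 19 villages in Sepone and 165 from the 18". The last of these counts belongs to the control district, Vilabuly.
- **Variables.** Residence in an intervention or control village is one of two main predictors. The secondary outcome is hours of postpartum stay at the facility, and no model is named for it.

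**The concern.** A design effect of 2 means that the authors expect women in the same village to resemble each other enough to double the variance of an estimate. Pearson's chi-square and the ordinary t-test compute their variance as if every woman were independent. Using the first assumption to plan the survey and the second to analyse it is inconsistent. It is also a choice the article makes in so many words, so it is not a detail left to a fuller plan.

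If the tests are run as named, some covariates will look associated with postnatal care uptake when they are not. The risk is greatest for factors that hardly vary inside a village. Those are the factors a reader of this study will care about: district of residence, access to a facility, ethnicity. Unadjusted differences in means or proportions for such factors would also be reported with intervals that are too short.

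**Working it through.** **Inputs from the article**
- Design effect (DEFF): 2. Nominal two-sided level: 0.05.
- Villages: 19 + 18 = 37. Expected women per round: 137 + 165 = 302.
- Mean women per village: m = 302/37 = 8.16.

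**Assumed, not in the article**
- ICCs of the covariates (ρx), shown over a range.
- A mean uptake of 15% in the simulations.
- How far a village's uptake level persists from baseline to end line, shown over a range.

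**Step 1. The plan's own sample size.** The sample-size paragraph expects this: "We anticipate a 15.0% increase in facility-based follow-up PNC in the intervention villages and a 5.0% increase in the control villages". The Results section adds "assuming baseline utilization is about 5% in both districts". That implies 20% against 10% at end line. The unpooled formula gives (1.960 + 0.842)² × (0.20×0.80 + 0.10×0.90)/0.10² = 196.2 per arm. With two arms, DEFF 2 and a factor of 1.1 for non-response, the total is 196.2 × 2 × 2 × 1.1 = 863, not 302. With 15% against 5% the formula gives 137.4 per arm. Then 137.4 × 2 × 1.1 = 302.2, which can be read as a two-arm total without the design effect or as a per-arm figure with it. How 302 arose is a separate question. Only the stated design effect is used below.

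**Step 2. ICC implied by the design effect.** DEFF = 1 + (m − 1)ρ, so ρ = (2 − 1)/(8.16 − 1) = 0.14.

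**Step 3. Factor constant within each village.** An unadjusted test uses a standard error that is too small by √DEFF.
- True size = 2 × P(Z > 1.96/√DEFF) = 2 × P(Z > 1.386) = 16.6%.
- Interval width relative to the correct width = 1/√2 = 0.71. Coverage = 100% − 16.6% = 83.4%.
- At a design effect of 1.5 the size would be 11.0%.
- Simulation of a chi-square by arm (20,000 runs, 37 villages, 137 against 165 women, beta-binomial outcome, ICC 0.14) gave 17.0%.

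**Step 4. Characteristic that varies within villages.** The effective inflation is DEFF = 1 + (m − 1)·ρy·ρx. Since (8.16 − 1) × 0.14 = 1.0, this is simply 1 + ρx.

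| Assumed ρx | Effective DEFF | True size, formula | Simulation |
|---|---|---|---|
| 0 | 1.0 | 5.0% | 4.9% |
| 0.1 | 1.1 | 6.2% | 6.2% |
| 0.3 | 1.3 | 8.6% | 8.4% |
| 0.5 | 1.5 | 11.0% | not run |
| 1 (fixed in village) | 2.0 | 16.6% | 17.0% (arm) |

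**Step 5. Crude difference-in-differences, if it were tested without adjustment.** The same villages are surveyed twice, so stable village differences cancel. The size therefore depends on the between-round correlation of village levels. Simulation (20,000 runs, 137 + 165 women per round, ICC 0.14) gave about 17% at correlation 0, about 10% to 11% at 0.5, 5% at 0.9 and just under 4% at 1. At ICC 0.05 the range was about 9% down to about 4%. Such a test can be too liberal or slightly conservative.

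**The case against.** The strongest reply is that the quoted sentence does not test the intervention. It describes bivariate comparisons by women's characteristics, listed before the multivariable model. Many of those characteristics vary within villages, so the inflation is modest. The effectiveness claim rests on a mixed-effects model, which can carry village clustering. A condensed article may also leave cluster-adjusted variants to a fuller plan.

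Most of this stands, and it limits the point. It rules out four stronger readings that a reader might infer:

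- *Every 5% test in the study runs at about 17%.* That figure belongs to factors fixed at village level. Step 4 shows far less for most individual characteristics.
- *The primary result is invalid.* The mixed-effects logistic model is the stated tool for that effect. The article does not name the level of its random effect, but that is a detail for the analysis plan and no ground for calling its p-value wrong.
- *The difference-in-differences will be an unadjusted z test, and hours of stay will be compared by t-test.* The z test appears only in the sample-size calculation, and the Data analysis section assigns no test to stay. Both are open, not wrongly fixed.
- *All intervals are too narrow.* A chi-square test yields no interval. The factor of 0.71 concerns unadjusted differences between village-level groups at the full design effect.

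What the reply does not remove is that the article names two independent-observation tests, sets a p<0.05 threshold and assumes a design effect of 2. An unnamed test can be left to a later plan; a named test that conflicts with the stated variance assumption should be corrected.

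**Conclusion.** The point holds for the bivariate comparisons. If run as named, their p-values are miscalibrated to a degree that depends on how strongly the covariate clusters by village. The size is up to about 16.6% for arm of residence and other village-level factors, and about 5% to 9% for covariates with an ICC of 0 to 0.3. That facility access and ethnicity lie near the village-level end is plausible, but the article does not show it.

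The size rests on the plan's own design effect of 2 for uptake. If the true design effect is smaller, so is the inflation. Nothing in the article says that 2 also holds for hours of stay, so the 16.6% carries over to an unadjusted comparison of stay by arm only under that assumption. For the crude difference-in-differences, the direction and size of any error depend on how stable village levels are between rounds: about 17% to 4% at ICC 0.14. The point is worth correcting, but it does not undermine the primary intervention effect.

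**What to change.** In the Data analysis section:

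1. Replace the Pearson chi-square with a Rao-Scott chi-square, with village as the primary sampling unit.
2. Replace the t-tests with regression using village-clustered standard errors.
3. State that the crude difference-in-differences uses village-clustered inference. A t reference with 37 − 2 = 35 degrees of freedom is a reasonable choice for this number of villages.
4. Name a group-by-time model with village-clustered inference for hours of postpartum stay.

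The Stata release already specified supports all of this, and data collection does not change. The cost is a few sentences, a few software options and, for most comparisons, wider intervals. Some covariate associations that an unadjusted test would call significant will no longer be so. The wording should be settled before the end-line data, planned for around July 2026, are seen.
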